# Protocol of a randomised delayed-start double-blind placebo-controlled multi-centre trial for Levodopa in EArly Parkinson’s disease: the LEAP-study

**DOI:** 10.1186/s12883-015-0491-1

**Published:** 2015-11-19

**Keywords:** Parkinson’s disease, Levodopa, Randomised delayed-start placebo-controlled trial, Disease modifying

## Abstract

**Background:**

The aim of this study is to investigate if early treatment with levodopa has a beneficial disease modifying effect on Parkinson’s disease (PD) symptoms and functional health, improves the ability to (maintain) work, and reduces the use of (informal) care, caregiver burden, and costs. Additionally, cost-effectiveness and cost-utility of early levodopa treatment will be assessed.

**Methods:**

To differentiate between the direct symptomatic effects and possible disease modifying effects of levodopa, we use a randomised delayed-start double-blind placebo-controlled multi-centre trial design. Patients with early stage PD whose functional health does not yet necessitate initiation of PD-medication will be randomised to either 40 weeks of treatment with levodopa/carbidopa 100/25 mg TID including 2 weeks of dose escalation or to 40 weeks placebo TID. Subsequently, all patients receive levodopa/carbidopa 100/25 mg TID for 40 weeks. There are 8 assessments: at baseline and at 4, 22, 40, 44, 56, 68, and 80 weeks. The primary outcome measure is the difference in the mean total Unified Parkinson’s Disease Rating Scale scores between the early- and delayed-start groups at 80 weeks. Secondary outcome measures are rate of progression, the AMC Linear Disability Score, side effects, perceived quality of life with the Parkinson’s Disease Questionnaire-39, the European Quality of Life-5 Dimensions (EQ-5D), ability to (maintain) work, the use of (informal) care, caregiver burden, and costs. 446 newly diagnosed PD patients without impaired functional health need to be recruited in order to detect a minimal clinical relevant difference of 4 points on the total UPDRS at 80 weeks.

**Discussion:**

The LEAP-study will provide insights into the possible disease modifying effects of early levodopa.

**Trial registration:**

ISRCTN30518857, EudraCT number 2011-000678-72

## Background

Parkinson’s disease (PD) is a neurodegenerative disease characterised by the progression of bradykinesia, tremor, and rigidity, as well as a wide range of non-motor symptoms. The core motor symptoms are caused by the degeneration of dopamine producing neurons [1, 2]. The mainstay of the treatment consists of dopamine replacement either with the dopamine precursor levodopa or with directly acting dopamine receptor agonists (DA).

Although levodopa is inexpensive and very efficacious [3, 4], many neurologists tend to delay initiation and timely adjustments of levodopa. One concern is that levodopa could be toxic, although this has never been supported by the results of clinical studies [5]. Another reason is the concern for side effects such as dyskinesias [1, 6]. Although levodopa-sparing strategies indeed delay the onset of dyskinesias compared to levodopa monotherapy, sooner or later all patients need levodopa [2]. The results of the ELLDOPA study suggest that levodopa may have a beneficial disease modifying effect in addition to the well-known direct symptomatic effect [3]. To date, other studies concerning disease modifying effects of dopaminergic drugs have been inconclusive or negative [7]. More knowledge of possible disease modifying effects of levodopa may improve the use of levodopa in daily clinical practice.

Therefore, we aim to investigate whether the early start of levodopa has a beneficial disease modifying effect on PD symptoms and functional health, subsequently improves patient’s quality of life and the ability to (maintain) work, and reduces the use of (informal) care, caregiver burden and costs. We will also assess cost-effectiveness and cost-utility of early levodopa treatment.

## Methods

### Trial design

To differentiate between the direct symptomatic effects and possible disease modifying effects of levodopa, we use a randomised delayed-start double-blind placebo-controlled design (Figs. 1 and 2). Seven academic hospitals and 43 community hospitals in the Netherlands are recruiting patients. Study nurses are trained to perform all study procedures.

**Fig. 1 Fig1:**
[figure not shown]
Delayed-start design. Studies with a delayed-start design investigate two agents: active treatment (*solid line*) and controlled treatment (*dashed line*). In phase 1, patients are randomised to either active (levodopa) or controlled (placebo) treatment. In phase 2, both groups receive active treatment

**Fig. 2 Fig2:**
[figure not shown]
Delayed-start design with beneficial effect of early treatment with levodopa. If a beneficial disease modifying effect of levodopa exists, patients in the early-start group will perform better at the end of the study than patients in the delayed-start group if phase 1 is sufficiently long and if the beneficial disease modifying effect is maintained during phase 2. The small improvement of the delayed-start group at the start of phase 1 and of the early-start group at the start of phase 2 represents the placebo-effect

### Study participants

The inclusion criteria are (a) idiopathic PD with bradykinesia and at least two of the following signs: resting tremor, rigidity or asymmetry; (b) newly diagnosed PD within the past two years; (c) age 30 years and older; (d) a life expectancy of more than two years; and (e) no limitations in functional health for which the patient needs PD-medication. Exclusion criteria are (a) tremor as most prominent symptom, such as a severe resting tremor that is present almost continuously or a tremor of medium to large amplitude which results in functional disability, such as interfering with feeding; (b) previous treatment with PD-medication; (c) cognitive impairments, defined as a Mini Mental State Examination (MMSE) of 23 points or lower; (d) a score of more than 28 points on the Beck Depression Inventory II (BDI-II); (e) diagnosis of depression by a psychiatrist in the last year; (f) history of psychosis; (g) the presence of signs indicating atypical or secondary parkinsonism; (h) untreated closed-angle glaucoma; (i) alcohol abuse; (j) possible pregnancy; (k) legally incompetent adults, and (l) inability to provide written informed consent.

### Study procedures and randomisation

If a patient is eligible, the neurologist briefly introduces the study and asks the patient permission to send contact information to the coordinating research nurse at the central study hospital (Academic Medical Center, University of Amsterdam). The neurologist provides the patient with written information about the study and informs the research nurse at the central study hospital. Subsequently, the research nurse in the central study hospital registers the patient in the Local Logistics Database. There are five research nurses in five study hospitals based throughout the Netherlands (Academic Medical Center, Atrium-Orbis Medical Center Heerlen/Sittard, Leiden University Medical Center, University Medical Center Groningen, and Radboud University Medical Center). After the patient has been registered, the research nurse based closest to the hospital from where the patient has been put forward is informed. Within three days, the research nurse contacts the patient by phone to answer questions about the study and the nurse makes an appointment to further explain the study if necessary. Patients are required to give a written informed consent to participate.

There are eight assessments, which take place at baseline, four weeks, 22 weeks, 40 weeks, 44 weeks, 56 weeks, 68 weeks, and 80 weeks – respectively Visits 1 to 8. At the end of Visit 1, patients are randomised to 40 weeks treatment with levodopa/carbidopa (early-start group) or to 40 weeks placebo (delayed-start group). The first 40 weeks of the study is called phase 1. Subsequently, all patients receive 40 weeks levodopa/carbidopa – phase 2 (Fig. 1).

Patients in the early-start group take levodopa/carbidopa capsules according to a starting-schedule during weeks 1 and 2, followed by levodopa/carbidopa 100/25 mg tablets TID during weeks 3 to 40 (Table 1). In weeks 41 and 42, they take levodopa/carbidopa 100/25 mg capsules TID. Patients in the delayed-start group take placebo capsules TID during the first 2 weeks, followed by placebo tablets TID during weeks 3 to 40. In weeks 41 and 42, they take levodopa/carbidopa capsules according to a starting-schedule (Table 1). From weeks 43 to 80, all patients receive the levodopa/carbidopa 100/25 mg tablets through their regular pharmacies. In the first 42 weeks of the study, the placebo capsules and tablets are identical in appearance, smell, and taste compared to the levodopa/carbidopa capsules and tablets; they are produced by ACE Pharmaceuticals (Zeewolde, The Netherlands) according to Good Manufacturing Practice guidelines.

**Table 1 Tab1:** Treatment schedule weeks 1 to 80

		Early group			Delayed group		
		Morning	Noon	Evening	Morning	Noon	Evening
Phase 1	Week 1 (capsules)	50/12.5	Placebo	50/12.5	Placebo	Placebo	Placebo
	Week 2 (capsules)	100/25	50/12.5	50/12.5	Placebo	Placebo	Placebo
	Weeks 3 to 40 (tablets)	100/25	100/25	100/25	Placebo	Placebo	Placebo
Phase 2	Week 41 (capsules)	100/25	100/25	100/25	50/12.5	Placebo	50/12.5
	Week 42 (capsules)	100/25	100/25	100/25	100/25	50/12.5	50/12.5
	Week 43 to 80 (tablets)	100/25	100/25	100/25	100/25	100/25	100/25

Doses are written as levodopa/carbidopa milligram

If the treating neurologist finds that the patient needs additional treatment during the placebo-controlled phase, the patient immediately starts with the capsules initially designated for weeks 41 and 42 and subsequently will use levodopa/carbidopa 100/25 mg TID. This means that - irrespective of initial treatment allocation – the patient is certain to take levodopa/carbidopa from that moment on. Patients that subsequently require additional treatment will receive levodopa/carbidopa 200/50 mg TID. If a patient needs more treatment, the choice and dose of additional medication is left to the discretion of the treating neurologist. If a patient does not follow the study protocol, this is registered; we aim to perform all further procedures and measurements according to the study protocol.

Randomisation is performed by a central website based computer program in 1:1 ratio (Fig. 1) and stratified by type of hospital (university medical centre versus non-university medical centre), age (below 65 years or 65 years and older), and symptom duration (shorter than 0.5 year or 0.5 year and longer), using variable permuted blocks. Study personnel, research nurses, neurologists, and patients are blinded to the treatment allocation at all times. ACE Apothecary (ACE Apotheek, Zeewolde, The Netherlands) allocates the randomised patient to a medication number that corresponds with the treatment group and ACE Apothecary is responsible for packaging, labelling and shipment of the study medication during the first 42 weeks of the study. Randomisation data are kept strictly confidential and are accessible only to authorised persons at ACE Pharmaceuticals and ACE Apothecary until the database is unlocked at the end of the study. All data will be entered in a central website based database before the database is unlocked.

Approval of the medical ethical committee of the Academic Medical Center was obtained. The LEAP-study is conducted according to the principles of the Declaration of Helsinki (version 2008). Study monitoring and data management are performed in accordance with the International Conference on Harmonisation - Good Clinical Practice guidelines. This is an investigator-initiated study. None of the funding organisations has influence on the design or execution of the trial, the analysis of the study data, or the publication of articles concerning the study data.

### Outcome measures

The primary clinical outcome measure is the difference in the mean total Unified Parkinson’s Disease Rating Scale (UPDRS) scores between the early- and delayed-start groups at 80 weeks (Table 2) [8]. Secondary endpoints are (a) progression of symptoms between Visit 2 and Visit 4 (phase 1) and between Visit 5 and Visit 8 (phase 2) measured with the UPDRS; (b) disability measured with the AMC Linear Disability Score (ALDS), defined as the between-group difference at 80 weeks (Table 2) [9]; (c) between-group difference in mean total UPDRS scores at 80 weeks and the progression of UPDRS scores during phases 1 and 2 in patients who followed the study ‘per protocol’; (d) between-group difference in mean total UPDRS scores at 80 weeks and the progression of UPDRS scores during phases 1 and 2 in patients with UPDRS scores in the highest quartile of scores at baseline who followed the study ‘per protocol’; (e) number of patients that need additional medication during phases 1 and 2; (f) cognitive impairment, measured with the MMSE (Table 2) [10]; (g) depression, measured with the BDI-II (Table 2) [11]; (h) perceived quality of life measured with the Parkinson’s Disease Questionnaire-39 (PDQ-39) (Table 2) [12]; (i) quality adjusted life years (QALY), after applying existing scoring algorithms to derive health utilities from observed European Quality of Life-5 Dimensions (EQ-5D) data (Table 2) [13]; (j) working status and absence from paid work measured with a standardised questionnaire; (k) caregiver burden with a standardised questionnaire; (l) resource utilisation outside of the participating hospitals measured with a standardised questionnaire (for (j), (k) and (l) we used an adjusted version of the Short Form - Health and Labour Questionnaire [14, 15] and iMTA Valuation of Informal Care Questionnaire targeted at the study population [16]); (m) costs per unit decrease of the UPDRS and costs per QALY [17, 18]; (n) number of patients withdrawn from the study or lost to follow up; (o) dyskinesias, measured with items 32 to 35 of the UPDRS part IV; (p) levodopa-induced motor response fluctuations throughout the course of the study measured with items 36 to 39 of the UPDRS part IV and three standardised questions concerning wearing-off phenomena (q) (serious) adverse events defined as the frequency, severity, nature, and duration of any adverse event throughout the course of the study.

**Table 2 Tab2:** Clinical rating scales

Clinical rating scale	Domain	Best score	Worst score
UPDRS	Parkinsonism	0	199
MMSE	Cognition	30	0
BDI-II	Depression	0	63
ALDS	Disability	100	0
EQ-5D	Quality of life	-	-
PDQ-39	Quality of life	0	100

*UPDRS* Unified Parkinson’s Disease Rating Scale, *MMSE* Mini Mental State Examination, *BDI-II* Beck Depression Inventory II, *ALDS* AMC Linear Disability Scale, *EQ-5D* European Quality of Life-5 Dimensions, *PDQ-39* Parkinson’s Disease Questionnaire-39

### Statistics

Based on the ELLDOPA study, we assume a mean baseline UPDRS score of 28 points with a standard deviation of 13 points and anticipate a mean UPDRS score in the early-start group of 31 points (worsening of 3 points during follow-up) and a mean UPDRS score in the delayed-start group of 35 points (worsening of 7 points) at the final outcome assessment at 80 weeks [3]. Assuming that the common standard deviation is 13, a sample size of 167 in each group will have 80 % power to detect a difference in mean follow-up scores of 4 points, using a two-group *t*-test with a 0.05 two-sided significance level. In the ELLDOPA study, a dropout rate of 22.2 % was reported in the placebo group [3]. After 80 weeks, the ADAGIO-study reported a total dropout rate of 24.4 % in the 1 mg delayed-start group and 19.2 % in the 2 mg delayed-start group. Based on these results, a total withdrawal rate of 25 % was considered realistic [19]: therefore, we plan to include 223 patients per treatment arm, which means 446 patients in total (Fig. 3).

**Fig. 3 Fig3:**
[figure not shown]
Flow chart LEAP-study. Taking into account a withdrawal rate of 25 %, 446 patients need be enrolled to be able to show a minimal clinically relevant difference of four points on the total UPDRS at the end of the study

Data will be analyzed according to the intention-to-treat principle. The main analysis of this trial consists of a comparison between the trial treatment groups of the primary outcome after 80 weeks. First, the follow-up difference of mean UPDRS scores between the treatment arms will be crudely analyzed using a two-group *t*-test. Second, the UPDRS follow-up scores will be further investigated using analysis of covariance (ANCOVA), taking into account patients’ UPDRS baseline values. To account for the repeated measures within patients, a random effects model will be used.

With regard to the comparisons of the secondary outcome progression of symptoms during phases 1 and 2 we planned two separate analyses using a random effects model to account for the repeated measures within patients (Fig. 2). For phase 1, we will use the measurements of Visit 2 (4 weeks), Visit 3 (22 weeks) and Visit 4 (40 weeks) to estimate the difference in slopes between the two treatment groups. A more progressive course (steeper upward slope) in the placebo group during phase 1 can reflect disease-modifying effects of levodopa. This will be further explored by examining the slopes of phase 2. Equal steepness of the slope during phase 2 indicates that the (assumed) effect found in phase 1 is a true disease-modifying effect. Therefore, we will use measurements of Visit 5 (44 weeks), Visit 6 (56 weeks), Visit 7 (68 weeks), and Visit 8 (80 weeks) to test equality of progression in phase 2 with a non-inferiority test on the difference between the slopes of the two treatment arms using a non-inferiority margin of 0.055 UPDRS points difference in increase per week (Fig. 2). The slopes of the phases 1 and 2 will be analysed by both an intention-to-treat and a per-protocol approach (see below for further explanation).

As pointed out earlier, the main outcome in this study will be the comparison between treatment arms on UPDRS scores after the total study period of 80 weeks, since this outcome relates to clinical practice. A difference of four points on the total UPDRS is considered to be clinically relevant [20]. The comparisons of slopes in the secondary analyses serve only to differentiate between the different types of treatment effects (direct symptomatic vs disease modifying). Here we pre-specify the possible inference made on these secondary analyses:if a faster progression is found in the placebo group during phase 1 and the non-inferiority assumption assuming equal progression is met in phase 2, this will be indicative of a true disease-modifying effect;if a faster progression is found in the placebo group during phase 1, but non-inferiority of slopes during phase 2 is not demonstrated, then the results are indicative of only direct symptomatic effects.

With regard to the comparisons of the other secondary outcomes (disability, number of patients that need additional medication for PD, cognitive impairment, mood, quality of life, ability to (maintain) work, use of (informal) care, caregiver burden, levodopa-induced response fluctuations, and side effects), we will use the appropriate parametric and nonparametric statistics. Cost-effectiveness and cost-utility analyses will be performed from a societal perspective with the costs per unit decrease on the UPDRS respectively, the costs per QALY as outcomes. In all analyses statistical uncertainties will be expressed in 95 % confidence intervals.

Subgroup analyses by type of hospital (university medical centre versus non-university medical centre), age and disease duration will be performed. Finally, two additional ‘per protocol’ analyses will be carried, focusing on (a) between-group difference in UPDRS scores at 80 week and the progression of UPDRS scores during phases 1 and 2, and (b) between-group difference in UPDRS scores at 80 weeks and the progression of UPDRS scores during phases 1 and 2 in patients in the highest quartile of scores at baseline. Patients will be excluded from the per protocol analysis if they needed additional PD-medication during the study, if they did not use the correct dose and type of medication (e.g., extended release levodopa formulations), or if they missed either Visits 1, 2, 4, 5 or 8.

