Third, the placebo-controlled phase of 40 weeks was chosen based on the results of the ELLDOPA study, which suggested a possible disease modifying beneficial effect of levodopa evident after 40 weeks of treatment [3]. Ideally, the placebo-controlled phase of 40 weeks would even be longer because if a disease modifying effect of levodopa exists, there would then be more time for the slopes of the two treatment groups to diverge further (Fig. 2). However, because of symptom progression, a placebo-controlled phase of more than 40 weeks would result in the retention of progressively fewer patients in the placebo-controlled phase of the study, making the placebo-controlled phase only slightly longer because of the increasing lower numbers in the delayed-start group – thereby diminishing the theoretical advantage of a longer placebo-controlled phase. More importantly, poorer retention in the delayed-start group would compromise the ability to show a difference between the two groups and would potentially select out patients with a milder or more slowly progressive disease course, thereby diminishing a possible existing difference between the two groups. Also, a longer placebo-controlled phase would result in higher costs in this investigator-initiated study. A study design with an additional delayed-stop (at 40 weeks) arm was rejected because this would require patients that typically need antiparkinson medication at this point would experience increased disability and discomfort due to having treatment withheld.

Fourth, we chose a daily levodopa/carbidopa dose of 300/75 mg. In the ELLDOPA study, three levodopa/carbidopa doses (150/37.5 mg, 300/75 mg or 600/150 mg daily) were tested and compared with placebo for 40 weeks, followed by a two-week washout period. The results suggested a beneficial disease modifying effect of levodopa in all treatment groups, thereby making a strong case to choose the 150/37.5 mg daily dose for the current study. However, in the 150/37.5 mg group, there was also a higher dropout rate [3]. We considered a daily treatment of levodopa/carbidopa 600/150 mg too high because of the risk of more side effects [24] and because in daily practice, starting-doses of levodopa are usually lower.

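### The intention-to-treat week-80 analysis leads with a crude t-test that, without imputation, omits patients with no week-80 score, while the random effects model that could keep them is left unranked

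*Protocol article*

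**What the plan says.** All references are to the protocol article.

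- **Methods, Statistics (text after the Fig. 3 legend).** The principle is "Data will be analyzed according to the intention-to-treat principle". The main analysis compares the arms on the primary outcome at 80 weeks. The steps are given in order: "First, the follow-up difference of mean UPDRS scores between the treatment arms will be crudely analyzed", by a two-group t-test; second, an ANCOVA with baseline UPDRS; and then "To account for the repeated measures within patients, a random effects model will be used". That last sentence states neither the visits it covers nor its standing against the first two steps. The slope models for phases 1 and 2 are described separately in the next paragraph.
- **Methods, Statistics (sample size).** The calculation is for the two-group t-test: "a sample size of 167 in each group will have 80 % power". Withdrawal of 25% is assumed as one overall rate; "therefore, we plan to include 223 patients per treatment arm".
- **Methods, Statistics (per-protocol rule).** Missing Visit 8 (week 80) is one of the grounds for exclusion from the per-protocol analysis.
- **Methods, Study procedures and randomisation.** Patients who do not follow the protocol are registered, and the aim is to carry on with all their later measurements. There are seven post-baseline visits, at weeks 4, 22, 40, 44, 56, 68 and 80.
- **Discussion (third design point).** In arguing against a placebo phase longer than 40 weeks, the authors say that "poorer retention in the delayed-start group would compromise the ability to show a difference between the two groups", and that it could leave a milder or slower-progressing group behind.

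**The concern.** A t-test on week-80 scores needs a week-80 score. Unless missing scores are imputed, a patient who leaves after, say, week 56 contributes nothing, although several UPDRS scores are on file. The same is true of an ANCOVA on the week-80 score. For a patient who misses Visit 8, the intention-to-treat t-test and the per-protocol analysis then come to the same thing: both leave the patient out.

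Enrolling 223 to keep 167 protects precision. It does nothing about who is lost. If patients with worse scores leave the delayed-start arm more often, or if loss there is more selective, the observed delayed-minus-early difference shrinks. The opposite pattern would inflate it. With a 4-point target and 80% power, a shift of 1 point matters to the trial's conclusion.

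The text also names three analyses of one outcome without saying which carries the conclusion. The first named is the least protected against selective loss, and the one best placed to use the partial data is the least defined.

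**Working it through.** **1. Reproduce the plan's figures.** Inputs from Methods, Statistics: difference 4, SD 13, 80% power, "with a 0.05 two-sided significance level", withdrawal 25%.

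- Normal approximation: n = 2 × (1.960 + 0.842)² × 13² / 4² = 165.8, so 166 per group.
- Noncentral t: 166.8, so 167 per group, with power 80.05% at 167. This agrees with the plan.
- Inflation: 167 / 0.75 = 222.7, so 223 per arm and 446 in total. This agrees with the plan.
- In reverse: 223 × 0.75 = 167.25. The t-test is sized on about 334 of 446 patients, and about 112 are assumed to give it no score. With all 223 per arm scored, power would be 90%.

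**2. Bias of a comparison limited to patients with a week-80 score.** Let d be the share lost in an arm and g the mean week-80 score of lost patients minus that of completers. The full-arm mean equals the completer mean plus d × g, so

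observed difference (delayed − early) = 4 − (d_delayed × g_delayed − d_early × g_early).

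The documents give neither d by arm nor g. The values below are assumptions. Power uses SD 13, arm sizes 223 × (1 − d) and the normal approximation.

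| Loss delayed / early | g delayed / early | Bias term | Observed difference | Power |
|---|---|---|---|---|
| 25% / 25% | 10 / 10 | 2.5 − 2.5 = 0 | 4.0 | 80% |
| 30% / 20% | 5 / 5 | 1.5 − 1.0 = 0.5 | 3.5 | 69% |
| 30% / 20% | 10 / 10 | 3.0 − 2.0 = 1.0 | 3.0 | 56% |
| 35% / 15% | 5 / 5 | 1.75 − 0.75 = 1.0 | 3.0 | 55% |
| 35% / 15% | 10 / 10 | 3.5 − 1.5 = 2.0 | 2.0 | 29% |
| 25% / 25% | 5 / 0 | 1.25 − 0 = 1.25 | 2.75 | 49% |

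The first row shows that loss as such is harmless to the contrast when it is equal and equally selective. The last row shows that equal percentages are not enough if selection differs between arms.

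**3. Cross-check by simulation: completers only.** With withdrawal rising by a logistic slope of 1 per SD of the last score, and a correlation of 0.5 to 0.7 between that score and week 80, the completer difference was 3.93 to 4.05 at 25%/25%, 3.33 to 3.44 at 30%/20%, and 2.58 to 2.98 at 35%/15% (delayed/early). These lie close to, or within, the ranges in the table.

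**4. Completers against all visits.** A second simulation used 400,000 per arm, assumed visit means reaching 35 and 31 at week 80, and the same rule in both arms linking withdrawal to the last observed score.

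| Dependence on last score | Loss delayed / early | True difference | Completers | All visits |
|---|---|---|---|---|
| None | 23.5% / 23.4% | 4.01 | 4.02 | 4.02 |
| Moderate | 26.4% / 23.1% | 4.03 | 3.79 | 4.04 |
| Stronger | 33.0% / 26.6% | 3.98 | 3.22 | 3.96 |

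Here loss is missing at random by construction, which is the condition under which an all-visits likelihood analysis is valid. The table shows what is gained if that condition holds. It does not show that it holds.

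**The case against.** The case on the other side is substantial.

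- **A random effects model is already in the main-analysis paragraph.** This stands. Fitted to all visits, it would keep patients with partial data, and the plan itself calls the t-test crude. But the visits and the rank are not stated, and the powered analysis is the t-test, so a reader will take the t-test as the lead.
- **The Discussion does not predict selective loss in this trial.** This stands too. A reader might infer from "poorer retention in the delayed-start group would compromise the ability to show a difference between the two groups" that the authors expect faster progressors to drop out of the delayed arm. The sentence concerns a placebo phase of more than 40 weeks and explains why 40 was chosen. It describes a mechanism, not a forecast.
- **Needing treatment is not being lost.** Patients who need more treatment in phase 1 move on to levodopa under blinding, and the protocol aims to keep measuring those who deviate. If that succeeds, the faster progressors will have week-80 scores and the bias will be small. It is an aim, however, and the sample size still allows for 25% withdrawal.
- **The arm-specific losses are assumed.** This is correct. The cited rates (22.2%, 24.4%, 19.2%) all come from placebo or delayed-start groups and say nothing about imbalance. Loss through side effects in the early arm could act in the other direction.
- **Missing-data rules belong in the full protocol or analysis plan.** Agreed, and their absence from the article is not the point here. Imputation before the t-test is possible. The point is the stated choice and order of methods.

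**Conclusion.** The point holds in limited form. The article declares intention-to-treat, leads with an unadjusted week-80 t-test, sizes the trial on that test after removing withdrawals, and leaves the random effects model undefined and unranked. Without imputation, the lead test and a week-80 ANCOVA discard the earlier visits of patients with no week-80 score, and the t-test also makes no use of baseline.

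A reader might go further and conclude that the primary result will be biased, or that a completers' analysis is being passed off as intention-to-treat. The documents do not support that: the bias is conditional, a suitable model type is already named, and continued measurement is intended.

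The size rests on assumption. If loss is 10 to 20 percentage points higher in the delayed arm and lost patients are 5 to 10 points worse than completers in both arms, a true 4 points becomes 3.5 to 2.0. If loss is equal and equally selective, the effect on the difference is nil. The sample-size arithmetic is correct. This is a change that should be made, not a fatal flaw.

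**What to change.** State one primary analysis: the week-80 treatment contrast from a repeated-measures mixed model including all randomised patients with any post-baseline UPDRS score (weeks 4 to 80), with treatment-by-visit terms and adjustment for baseline UPDRS. Analyse patients in the arm to which they were randomised. Present the week-80 t-test and ANCOVA as supportive analyses of patients with a week-80 score.

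The target quantity, the difference in mean total UPDRS at 80 weeks, does not change. Nor do the visits, the conduct or the 446 patients. The cost is a change of wording, since the data are already collected and the type of model is already mentioned.

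The drawback is that the model relies on missing at random. That is generally weaker than what the t-test on completers needs, namely loss unrelated to outcome within each arm or selection that happens to cancel (equal d × g). It cannot be verified from the data, so a sensitivity analysis that lets unobserved week-80 scores depart from it, by different amounts in the two arms, is advisable. Reporting the number without a week-80 score by arm, with their last observed UPDRS, would let readers judge how much rests on it.
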